### **Triage theory regarding vitamin K**

During times of scarcity, micronutrients are reserved for use in processes that form the greatest threat to short-term survival if not properly executed [14]. With regard to vitamin K insufficiency, it appears to be preferentially transported to the liver for the activation (via carboxylation) of procoagulant factors at the expense of extrahepatic vitamin K-dependent proteins such as MGP and protein S (figure 1) [15].

This was demonstrated in women between 60 and 80 years old who consumed a vitamin K1 deficient diet for 28 days. Undercarboxylated osteocalcin, a vitamin K-dependent bone protein, increased almost immediately, whereas undercarboxylated factor II increased more slowly [15]. Moreover, when patients using vitamin K antagonists (VKA) as anticoagulants steadily increased their dietary intake of vitamin K1, a significant decrease in undercarboxylated factor II was seen at 150 µg/day, while a significant decrease in undercarboxylated osteocalcin was only seen at an intake 300 µg/day [16].

Similar to osteocalcin and MGP, vitamin K insufficiency would result in deficient activation of endothelial protein S before causing a decrease in carboxylated prothrombin [17]. This could explain the seemingly paradoxical increase of thrombosis risk in the first week of treatment with VKAs [18].

### **Assessment of vitamin K status**

Measuring circulating levels of the two naturally occurring forms of vitamin K – vitamin K1 (phylloquinone) and K2 (the group of menaquinones) – is technically feasible. However, the value of such measurements is limited. Quantification of vitamin K-dependent proteins that have not been carboxylated, on the other hand, is a valuable method reflecting the combined functional deficit of vitamin K1 and K2. Determination of desphospho-uncarboxylated (dp-uc; i.e. inactive) MGP levels as well as the ratio between uncarboxylated and carboxylated osteocalcin are validated assays of extrahepatic vitamin K status [19].

Dp-ucMGP is a robust biomarker of extrahepatic vitamin K status. High dp-ucMGP reflects low vitamin K status and vice versa. Although increasing vitamin K consumption decreases dp-ucMGP [20-22], its levels are not simply a reflection of vitamin K intake but depend on other factors as well. Circulating dp-ucMGP concentration can best be regarded as a reflection of the total extrahepatic vitamin K deficit, i.e. the amount of vitamin K that is needed to carboxylate all the uncarboxylated vitamin K-dependent proteins in the body [23]. Hepatic vitamin K status is usually quantified by measuring levels of protein induced by vitamin K absence (PIVKA)-II (i.e. uncarboxylated prothrombin) [15].

## 1.2 Rationale for the current study

Recently, we found a reduced vitamin K status (as quantified by dp-ucMGP) in COVID-19 patients as compared to controls. In these patients, low vitamin K status was also associated with poor outcome (defined as the need for invasive ventilation or death) and accelerated elastic fiber degradation (quantified by plasma (iso)desmosine (DES) a byproduct of elastin degradation). In contrast, hepatic vitamin K status, measured by inactive factor II (also called protein-induced by vitamin K absence (PIVKA)-II) was unaffected in most patients (figure 2). Low dietary vitamin K intake and VKA use are evident causes of elevated dp-ucMGP in the general population [13, 24]. However, during COVID-19, inflammation causes pulmonary elastic fiber damage which could also lead to an upregulation of MGP and a draining of extrahepatic vitamin K. The significant correlation between increased dp-ucMGP levels, and elastic fiber degeneration and poor prognosis supports the theory that vitamin K insufficiency contributes to pulmonary pathology.

Though dp-ucMGP is elevated, hepatic pro-coagulant vitamin K status, quantified by measuring PIVKA-II, was hardly affected. Considering the preferential activation of hepatic-over extrahepatic proteins and the fact that about 50% of protein S synthesis and activation by vitamin K occurs in endothelial cells, this could increase the risk of coagulation. Consumption of clotting factors during thrombosis would put a further burden on vitamin K stores by increasing demand for activation of newly synthesised coagulation factors. With preference given to the carboxylation of pro-coagulant factors, progressive depletion of active endothelial protein S increasingly skews the balance towards coagulation.

Based on these finding and previous studies, we hypothesize that improving vitamin K-status by vitamin K supplementation could have favorable effects on both pulmonary damage and coagulation abnormalities in COVID-19 patients.

There is increasing evidence that vitamin K2 differs from vitamin K1 in terms of absorption, half-life and carboxylation efficiency, recently reviewed in [25]. In short vitamin K2, especially in the form of menaquinone-7 (MK-7), has a longer half-life and more potent activity in the carboxylation of vitamin K-dependent proteins. As a consequence most studies investigating the health benefit of vitamin K on outcomes for osteoporosis, atherosclerosis, cancer and inflammatory diseases have used vitamin K2 MK-7 [25].

[figure not shown]

**Figure 1:** (1) After absorption, vitamin K1 is preferentially transported to the liver via the portal circulation, where it is utilized for carboxylation of hepatic coagulation factors. This implies that during periods of vitamin K insufficiency, (2) the grade of carboxylation is usually higher for hepatic factor II (3) than for endothelial protein S in veins and pulmonary matrix Gla protein (MGP). Source: [26].

[figure not shown]

**Figure 2:** (A) Dp-ucMGP was measured in plasma of COVID-19 patients with a good outcome (discharge without invasive ventilation, n=75, orange) or poor outcome (invasive ventilation and/or death, n=60, red), compared to a cohort of controls. Open circles represent patients using VKA at admission. (B) PIVKA-II was measured in those patients not using

VKA (n=122). The detection threshold and normal range for healthy controls is shown in gray. **(C)** For all COVID-19 patients who were not dialysis dependent at admission with a good outcome (n=69, orange) or poor outcome (n=58, red) log-transformed baseline dp-ucMGP and desmosine values are shown, with open circles representing VKA users. Figures modified from [26].

## 2. OBJECTIVES

### Primary objectives:

- To evaluate the effect of oral vitamin K2 supplementation on elastic fiber degradation, as measured by plasma desmosine, during COVID-19 requiring hospital admission
- To evaluate the effect of oral vitamin K2 supplementation on extrahepatic vitamin K status, as measured by circulating dp-ucMGP, during COVID-19 requiring hospital admission

### Secondary objectives:

- To evaluate the effects of oral vitamin K2 supplementation on adverse events and disease progression during COVID-19 requiring hospital admission
- To evaluate the effects of oral vitamin K2 supplementation on hepatic vitamin K status, as measured by circulating PIVKA-II, during COVID-19 requiring hospital admission

### Exploratory objectives

- To evaluate the effect of vitamin K2 supplementation on circulating (undercarboxylated) protein S
- To evaluate the effect of vitamin K2 supplementation on respiratory failure requiring intubation and mechanical ventilation or leading to death
- To evaluate the effects of supplementation of vitamin K2 on disease severity on lung CT scan
- To evaluate the effect of vitamin K2 supplementation on active MGP concentrations
- To evaluate the effect of vitamin K2 supplementation on TFPI and normative APC sensitivity ratio and prothrombin (Echis Carinato test)
- To evaluate the effect of vitamin K2 on circulating MMP9
- To evaluate the effect of vitamin K2 on systemic inflammation by measuring cytokines and inflammatory mediators like interleukin-6 (IL6)
- To further explore the pathophysiology and biomarkers for COVID-19 susceptibility, severity and disease progression, including the Vitamin K epoxide reductase complex subunit 1 (VKORC-1) gene polymorphism and vitamin D receptor gene polymorphism

### 3. STUDY DESIGN

This is a double-blind, placebo-controlled randomized phase 2a intervention study in male and female patients over 18 years old with COVID-19 requiring supplemental oxygen and hospital admission. Patients will be treated with oral vitamin K2 or placebo from day 1 until discharge, with an expected average hospital stay duration of 6 days. After written informed consent is obtained from the patients or a legal representative, eligible patients will be randomized between the intervention (vitamin K2, in the form of menioquinone-7) and control (placebo) groups.

Patients randomized to the intervention group will take three tablets of vitamin K2 menaquinone-7 333mcg per day (for a total dose of 999mcg per day), from day 1 until day 14 or discharge, whichever occurs first, figure 3. Patients in the control group will receive a matched placebo. Adverse events will be collected daily and blood will be sampled three times a week until discontinuation of treatment. A low-dose chest CT scan will be made at admission and 5 days after treatment. If a patient is discharged before day 5 post treatment, a CT scan will be made before discharge. Mortality and serious adverse events will be followed up on day 28.

Patients will receive all routine treatment for COVID-19 according to general hospital practice.

[figure not shown]

**Figure 3:** Clinical trial design.

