**Nature and extent of the burden and risks associated with participation, benefit and group relatedness:**

Benefits: There is a potential benefit for participants in this study if vitamin K2 is shown to help prevent complications from COVID-19 disease. However, there is no preliminary causal evidence for this relationship. Participants will be randomized 1:1 in the study and intervention group, meaning only half will receive the intervention.

Risks and burdens: Risks for participants are related to three interventions: 1) taking vitamin K2, 2) repeated blood draws, 3) extra low-density CT scan(s). To date no adverse side-effects from oral vitamin K2 supplementation have been described in persons who do not use vitamin K antagonists (VKAs). However, there is no data on the use of vitamin K during COVID-19 disease. Blood will be drawn by venipuncture or through an intravenous cannula at regular time points as part of routine patient care. In study participants 25ml extra blood will be drawn every two days during admission. This volume is not expected to have consequences for the health of the patients. Finally, in participants one or two low dose CTs will be made outside routine care for COVID-19. The risks of this are expected to be minimal as the radiation exposure of a single low-dose CT is 1mSv.

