### 8.3.12 Study flow chart

|                                                                      | Inclusion      | Hospital admission |                    | Follow-up |
|----------------------------------------------------------------------|----------------|--------------------|--------------------|-----------|
| Study day                                                            | 1              | 2-14   | 15-27  | 28        |
| Eligibility criteria + informed consent                              | X              |                    |                    |           |
| Collection of demographic data and medical history                   | X              |                    |                    |           |
| Physical examination and vital signs                     | X              | X                  | X                  |           |
| Vitamin K2 MK-7 or placebo treatment                                 | X              | X                  |                    |           |
| Collecting (serious) adverse events                                  |                | as necessary       |                    |           |
| Collecting adverse events                                            |                | X                  |                    | X         |
| Laboratory testing                                     | X  | X                  | X                  |           |
| dp-ucMGP, PIVKA-II, desmosine                          | X  | X                  | X                  |           |
| Plasma and serum collection for exploratory endpoints  | X  | X                  | X                  |           |
| CT scan                                                              | X  | X      |                    |           |

 Vital signs are collected at least 3 times per day until discharge, physical examination is performed as necessary

 Blood is collected three times per week while the patient is admitted to the hospital

 Full blood count, electrolytes (sodium, potassium, calcium), creatinine, liver enzymes (bilirubin, ALAT, ASAT and LDH), c-reactive protein (CRP) and albumin; d-dimer will be determined at all follow-up time points (though not at baseline)

 Analysis performed retrospectively

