 Performed at baseline and on day 5, if patient is discharged before day 5 a CT scan is performed prior to discharge, if the CT scan cannot be made on day 5 it is made up to a maximum of 24 hours after day 5

 Number of study days dependent on discharge

 Or in the previous 24 hours

 Or in the previous 52 hours

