##### **8.4.1 Specific criteria for withdrawal**

Patients should be withdrawn from protocol treatment if any of the following criteria for withdrawal are met:

- Patient is not eligible to participate in the study in hindsight
- The occurrence of an adverse event preventing further treatment Patient becomes dialysis-dependent

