### **8.6 Follow-up of subjects withdrawn from treatment**

After discharge the investigator will follow-up the patients status as alive or deceased after 28 days after study intervention. If the patient is seen in outpatient clinic by a treating physician this information may be gathered from the patient's medical file. Alternatively, an investigator can call the patient's primary care physician or the patient at home to ascertain this information.

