## **10. STATISTICAL ANALYSIS**

All patients who receive at least one study treatment (the initial dose vitamin K2 or placebo) will be included in the intention-to-treat analysis.

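### Section 3 ends the primary-marker blood draws with treatment, while the flow chart continues them during admission; read literally, section 3 loses later values of patients who stop treatment in hospital

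*Protocol*

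**What the plan says.** Section 3 gives the sampling rule in the design overview: "blood will be sampled three times a week until discontinuation of treatment". The same section plans treatment "from day 1 until day 14 or discharge, whichever occurs first".

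The flow chart in 8.3.12 uses a different rule. The row for dp-ucMGP, PIVKA-II and desmosine is marked at inclusion, on days 2-14 and on days 15-27. The treatment row is empty for days 15-27. The footnote on the marker row reads "Blood is collected three times per week while the patient is admitted to the hospital", and the footnote on the day columns reads "Number of study days dependent on discharge". The burden paragraph of the Summary agrees with the flow chart ("25ml extra blood will be drawn every two days during admission"), and so does section 11.3.

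Treatment may end before discharge. Section 8.4 covers refusal and non-compliance, and section 8.4.1 adds mandatory reasons: "Patients should be withdrawn from protocol treatment if any of the following criteria for withdrawal are met". Those reasons are ineligibility found later, an adverse event that prevents treatment, and dialysis dependence. Section 8.4 also allows a patient to refuse treatment while agreeing to further data collection.

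Section 10 states that everyone who received at least one dose "will be included in the intention-to-treat analysis". Section 8.1.1 defines both primary endpoints by levels before and during supplementation, and section 8.2 places the primary assessment on the last day of treatment. Section 8.6, on patients withdrawn from treatment, says: "After discharge the investigator will follow-up the patients status as alive or deceased after 28 days after study intervention".

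**The concern.** The two sampling rules give different instructions for the primary markers in every patient whose treatment ends before discharge. Site staff cannot follow both.

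The early stop matters more. An intention-to-treat comparison needs outcome values regardless of whether treatment continued. If draws end with treatment, patients who stop contribute only values up to the stop, and the stop itself decides when their last measurement is taken. Two of the section 8.4.1 triggers, a treatment-preventing adverse event and dialysis dependence, may accompany worsening disease. Section 1.2 links high dp-ucMGP to poor outcome and to elastic fibre degradation, which desmosine measures. The lost values are therefore unlikely to be a random subset.

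This is a rule about collecting data. A statistical analysis plan can decide how to use values after an early stop, but it cannot recover samples that were never drawn.

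**Working it through.** **1. Where the rules diverge.** The phrase in section 3 can mean the moment this patient stops, or the scheduled end of treatment (day 14 or discharge). Both readings are set beside the flow chart.

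| Patient | Section 3, literal | Section 3, scheduled end | Flow chart |
|---|---|---|---|
| Discharged on treatment by day 14 | to discharge | to discharge | to discharge |
| Completes 14 days, still admitted | stops at day 14 | stops at day 14 | continues, up to day 27 |
| Taken off treatment early, still admitted | stops at withdrawal | to day 14 or discharge | to discharge, up to day 27 |

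The first row agrees throughout. The second conflicts under either reading. The third depends on the reading, and under the literal one the later values are lost.

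**2. What is lost.** Under section 10 an early stopper stays in the analysis set. The baseline sample and all draws before the stop remain. Only a patient who stops before the first post-baseline draw has no follow-up value at all.

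**3. The planned sample size (section 4.4).** Inputs: mean ln(pDES) 5.99, SD 0.603, difference 10% of 5.99 = 0.599, alpha 0.05 (two-sided assumed), power 80%.

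n per arm = 2 × [(1.960 + 0.842) × 0.603 / 0.599]² = 15.9, rounded up to 16. This reproduces the stated 16; the exact t-test gives 16.9, so 17.

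**4. Power if some patients have no usable post-baseline sample.** The protocol gives no in-hospital withdrawal rate, so a range is assumed.

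| Evaluable per arm | Share lost | Power, normal | Power, exact t |
|---|---|---|---|
| 20 | 0% | 88.1% | 86.5% |
| 18 | 10% | 84.6% | 82.5% |
| 17 | 15% | 82.5% | 80.2% |
| 16 | 20% | 80.2% | 77.6% |
| 14 | 30% | 74.8% | 71.6% |

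Power drops below 80% once more than about 15% (exact t) or 20% (normal approximation) are lost.

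**5. Possible shift in an arm mean, as an upper illustration.** Assume that a fraction f of one arm has no usable value, that those patients lie one SD above the rest, and that nothing offsets this in the other arm. The observed mean is then too low by f × 0.603.

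- f = 2/20: 0.060 ln units; exp(-0.060) = 0.94, or 6% lower; 0.060 / 0.599 = 10% of the planning difference.
- f = 4/20: 0.121 ln units; exp(-0.121) = 0.89, or 11% lower; 0.121 / 0.599 = 20% of the planning difference.

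Values drawn before the stop would shrink these figures.

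**6. The day 15-27 draws.** Thirteen days at three draws a week is 13/7 × 3 = 5.6, so 5 to 6 draws, or 125 to 150 ml at 25 ml each. This applies only to a patient admitted throughout; the expected average stay is 6 days.

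**The case against.** The strongest reply is that one overview sentence stands against the operational text. Sections 8.3.6 and 8.3.8 ask for samples three times a week with no stop at withdrawal, and the flow chart, the Summary and 11.3 all speak of admission. The protocol also uses discontinuation for the scheduled end: 9.5.1 attaches it to day 14, and 8.3.2 and 9.2.2 attach it to discharge. Early stopping is called withdrawal in 8.4 and 8.4.1. On that reading section 3 already says nearly what is needed. This is a fair reading but not a compelled one, and it leaves the day 15-27 conflict in place.

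A second reply is that the endpoints concern levels during supplementation, so values after an early stop are outside them just as day 15-27 values are. That stands, and it is why moving the draws is not enough: the protocol must also say that those values count.

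A reader might infer more than the protocol supports:

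- That patients who stop treatment drop out of the intention-to-treat comparison. They do not: section 10 keeps them in, with their earlier samples.
- That section 8.6 limits them to vital status while in hospital. Its sentence concerns the period after discharge.
- That the sickest patients are systematically removed. ICU admission does not end treatment (13.1 g) and tablets may be given by nasogastric tube (6.6), so many worsening patients would stay on treatment and be sampled.
- That the loss differs by arm. The trial is double-blind and no adverse effects are expected (13.1 j), so nothing in the protocol shows this, though it cannot be excluded.

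**Conclusion.** The sampling rules contradict each other and should be reconciled. For patients still in hospital after day 14 the conflict exists on any reading. For patients taken off treatment early it depends on how section 3 is read; on the literal reading they lose all later desmosine, dp-ucMGP and PIVKA-II values, and a comparison promised as intention-to-treat becomes an on-treatment one.

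The size is uncertain and probably small. No withdrawal rate is given, so the number affected cannot be derived. The shift of 0.06 to 0.12 ln units assumes a one-sided loss, a one-SD difference and no usable post-baseline value, and should be read as an illustration near the upper end, not an estimate. The protocol does not support a claim that the primary result is biased. It does support the claim that an avoidable and possibly informative loss of primary-marker data is left to the reader's choice between two rules.

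**What to change.** Adopt one rule and state it in section 3 and section 8.6: blood for desmosine, dp-ucMGP and PIVKA-II is drawn on the scheduled days up to day 14 or discharge, whichever is first, whether or not study treatment has been stopped, unless the patient withdraws consent for sampling.

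In the flow chart, either remove the marker draws for days 15-27 or label them exploratory and post-treatment, and bring the Summary and 11.3 into line.

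In section 8.1.1 or 10.1, say that values obtained after an early stop count in the intention-to-treat comparison. Without that sentence the endpoint wording would exclude them even though they were collected.

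The cost is protocol wording and a few more 25 ml samples in patients who have stopped treatment. The flow chart already schedules those draws.

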## 4. STUDY POPULATION

### 4.1 Population (base)

This study will enroll 40 male and female patients aged 18 years or older, who are admitted to the hospital with PCR-proven COVID-19 requiring supplemental oxygen.

### 4.2 Inclusion criteria

In order to be eligible to participate in this study, a subject must meet all of the following criteria:

- COVID-19 patients who are admitted to the CWZ with COVID-19 as primary reason for admission, with a laboratory confirmed SARS-CoV-2 infection within the previous 14 days
- Respiratory failure requiring supplemental oxygen, defined as requiring supplemental oxygen to sustain an arterial PO2  $\geq$ 70mmHg (measured by arterial blood gas) or an oxygen saturation of  $\geq$ 94% (measured using a pulse oximeter)
- At least 18 years old
- Able to safely swallow the study medication or possibility of safely administering this through a nasogastric tube
- Use of prophylactic heparin or LWMH according to hospital protocols, or use of therapeutic dosages if there is a medical indication for this
- Informed consent signed by patient

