#### Exploratory endpoints:

- Serum (undercarboxylated) protein S levels before and after vitamin K supplementation
- Incidence of respiratory failure defined as either intubation and mechanical ventilation or death (with respiratory failure as a likely direct or indirect cause of death) in the intervention versus control group
- Change in disease severity as measured by low-dose chest CT on day 5 and 10 versus baseline in intervention versus control groups
- Plasma levels of active MGP before and after vitamin K supplementation
- Normative APC sensitivity ratio and prothrombin (Echis Carinato test) and TFPI concentration before and after vitamin K supplementation
- Inflammatory parameters including CRP, d-dimer, ferritin, IL-6, TNF- $\alpha$ , IFN- $\gamma$  and s-IL-2r as measured by ELISA or Multiplex in both intervention and control groups
- Other markers related to the pathogenesis, susceptibility and severity of COVID-19 in both intervention and control groups
- Vitamin K epoxide reductase complex subunit 1 (VKORC-1) gene polymorphisms and vitamin D receptor gene polymorphisms

**Follow-up:** Clinical parameters, including symptoms, vital signs, grade 3 or 4 adverse events and serious adverse events will be collected daily during admission. Mortality will be determined 28 days after inclusion.

At baseline (up to 24 hours before treatment initiation) and subsequently three times a week (i.e. day 1, 3, 5 etc.) the following laboratory tests are performed immediately: full blood count, electrolytes (sodium, potassium, calcium), creatinine, c-reactive protein (CRP), and albumin. At each timepoint EDTA and citrate plasma, and serum will be frozen and stored at -80 degrees Celsius. At each time point (iso)desmosine (DES, a marker for elastin degradation, in EDTA plasma), dp-ucMGP (inversely associated with vitamin K status, in

EDTA plasma), PIVKA-II (inversely associated with vitamin K status, in serum) will be determined.

Further exploratory measurements can be performed on these, or a subset of these samples, including: (undercarboxylated)-protein S (measured by ELISA in citrate plasma), active MGP (measured by ELISA), prothrombin (Echis Carinatus test), TFPI (measured by ELISA in citrate plasma), normalized APC sensitivity ratio (nAPCsr) (protein S and TFPI activity), 25-OH vitamin D, plasma cytokines (i.e. IL-6, TNF- $\alpha$ , IFN- $\gamma$ ), soluble IL-2-receptor (s-IL-2r) and antibodies to SARS-CoV-2.

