Computed tomography (CT) is performed at baseline and on day 5 after study start for assessing pulmonary involvement score using published protocols. If patients are discharged before day 5 a second CT scan is made prior to discharge. Severity of Covid-19 pneumonia will be quantified and expressed as volume percentage of lung involvement on low dose chest CT by a specialized chest radiologist at University Medical Center Utrecht (UMCU).

At one point during the trial patient DNA will be collected using a mouth swab, for determination of the VKORC1 gene polymorphism.

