### **8.3.5 Clinical laboratory measurements**

At baseline (within 24 hours of admission) and subsequently three times per week, the following laboratory tests are performed: full blood count, electrolytes (sodium, potassium, calcium), creatinine, liver enzymes (bilirubin, ALAT, ASAT and LDH), c-reactive protein (CRP) and albumin. D-dimer will be performed at all follow-up time points (though not at baseline).

Arterial blood gas can be performed at the discretion of the treating physician but will not be part of routine measurements.

Performing additional laboratory analyses such as urinalysis, d-dimer, or cardiac enzymes in the context of standard patient care is at the discretion of the treating physician.

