#### **8.5 Replacement of individual subjects after withdrawal**

If a patient withdraws or is withdrawn before he or she has received the first treatment (vitamin K2 or placebo), he/she will be replaced with another suitable patient.

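### Both primary endpoints lack a blood draw at discharge, so a patient dosed on day 1 who leaves before day 3 gives a baseline value only, stays in the analysis set and is not replaced.

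*Protocol*

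**What the plan says.** Entry (Protocol 4.2) is open to "COVID-19 patients who are admitted to the CWZ with COVID-19 as primary reason for admission". The only time window among the entry criteria concerns the positive test: "with a laboratory confirmed SARS-CoV-2 infection within the previous 14 days". Patients must also have "Respiratory failure requiring supplemental oxygen, defined as requiring supplemental oxygen to sustain an arterial" oxygen or saturation target. The first dose follows inclusion directly, on study day 1, and treatment ends at discharge or day 14 (section 3, 8.3.2).

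The Summary sets the blood draws at baseline and "subsequently three times a week (i.e. day 1, 3, 5 etc". Section 3 stops sampling when treatment stops, and footnote 2 of the flow chart (8.3.12) limits it to the hospital stay. For a patient who leaves early, both mean that sampling ends at discharge. Section 3 describes treatment "with an expected average hospital stay duration of 6 days".

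For CT, an exploratory endpoint, the Summary adds: "If patients are discharged before day 5 a second CT scan is made prior to discharge". Section 3, 8.3.10 and the flow chart repeat this. Sections 8.3.6 (dp-ucMGP) and 8.3.8 (desmosine) have no equivalent rule for blood.

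Section 8.1.1 defines both primary endpoints by levels before and during supplementation. Section 10 puts every patient with one dose in the intention-to-treat set. Section 8.5 provides a replacement only "If a patient withdraws or is withdrawn before he or she has received the first treatment". Section 8.2 says that primary endpoint assessments finish on the last patient's last day of treatment.

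**The concern.** The protocol foresees discharge before a scheduled assessment and covers it for an exploratory endpoint, but not for the two primary ones. A patient with no on-treatment sample contributes nothing to a before-and-during comparison, and blood that was never drawn cannot be recovered by any analysis plan.

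The gap falls on a particular kind of patient. Those who leave before day 3 are the ones who recover fastest, so the sampled patients would be sicker on average than those randomised. With 40 patients in all, each lost outcome counts.

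**Working it through.** **1. Trace one patient through the schedule.** The first dose is on day 1 (8.3.2). The flow chart treats the day-1 sample as baseline, since footnote 7 allows it in the previous 24 hours. Even if the Summary's day-1 draw is read as a separate one, it falls on the day of the first dose. The next draw is on day 3. Discharge on day 2 ends treatment and sampling. The result is a baseline value, no on-treatment value, membership of the intention-to-treat set (section 10) and no replacement (8.5).

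**2. Compare with section 8.2.** An assessment on the last day of treatment would, for an early leaver, be an assessment at discharge. Neither the Summary, section 3, 8.3.6, 8.3.8 nor the flow chart contains such a draw. These places disagree.

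**3. Compare the baseline timing.** Section 8.3.5 has "At baseline (within 24 hours of admission) and subsequently three times per week"; 8.3.6 to 8.3.8 count the 24 hours from inclusion. These also disagree.

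**4. Reproduce the sample size (4.4).** Inputs: mean ln(pDES) 5.99, SD 0.603, a 10% difference read as 0.1 × 5.99 = 0.599, alpha 0.05 (taken as two-sided) and power 80%.

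n per group = 2 × (1.960 + 0.842)² × 0.603² / 0.599² = 15.9, so 16 per group and 32 in total. This matches the protocol. An exact t-test calculation gives 16.9, so 17 per group and 34 in total.

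**5. Margin for loss.** The stated allowance is 10% of 40 = 4 patients. The actual margin is 40 − 32 = 8 patients (20%), or 40 − 34 = 6 on the exact t-test.

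**6. Share leaving within 2 days of the first dose.** The only figure given is the 6-day mean stay; the spread is my assumption. With entry on the day of admission, the share is F(2), where F is the distribution function of stay with mean 6. For the exponential, for example, 1 − exp(−2/6) = 0.283.

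| Assumed spread, mean 6 days | Share before day 3 | Of 40 |
|---|---|---|
| Lognormal, sigma 0.5 | 2.6% | 1.0 |
| Gamma, shape 4 | 4.6% | 1.8 |
| Gamma, shape 3 | 8.0% | 3.2 |
| Lognormal, sigma 0.7 | 11.1% | 4.4 |
| Gamma, shape 2 | 14.4% | 5.8 |
| Lognormal, sigma 0.9 | 22.0% | 8.8 |
| Exponential | 28.3% | 11.3 |

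Four of the seven spreads exceed the allowance of 4; two exceed the margin of 8.

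**7. Power at the protocol's own effect, (40 − loss)/2 per group.**

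| Patients lost | Normal | t-test |
|---|---|---|
| 0 | 88.1% | 86.5% |
| 4 | 84.6% | 82.5% |
| 8 | 80.2% | 77.6% |
| 10 | 77.7% | 74.7% |
| 12 | 74.8% | 71.6% |

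The worst case in step 6, about 11 patients, lies between the last two rows.

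**The case against.** The strongest defence is that few patients will be affected. Everyone must still need supplemental oxygen at inclusion, which makes discharge the next day less likely. The high end of the range comes from an exponential stay, whose most likely value is zero days; that is a poor description of patients admitted in respiratory failure. Against the actual margin of 8, most of the assumed spreads do no harm to the planned power. All of this stands and limits the size of the problem. It does not supply the missing draw.

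A discharge sample after one or two doses may also show little effect. Section 6.3 reports changes in carboxylated osteocalcin in healthy volunteers after one day, but a near-maximal effect only by day 7. That too stands, although such a sample still gives a during-treatment value where there is otherwise none.

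Two stronger readings are tempting. First, because 4.2 sets no limit on days since admission and no minimum expected stay, a reader might infer that patients about to go home will be enrolled in numbers. With entry two days after admission, the assumed spreads do give about 24% to 36% (10 to 14 of 40). But section 3 places the first CT at admission, the flow chart accepts a baseline CT from at most 52 hours before, and 8.3.5 ties baseline laboratory tests to admission. None of these is an eligibility rule, but together they describe early entry, and nothing in the protocol suggests that late entry is common. Second, a reader might infer that the loss biases the comparison. That needs vitamin K2 to change discharge within about two days of the first dose in a double-blind trial. The protocol offers no evidence for this; loss of fast recoverers at the same rate in both arms does not by itself produce bias.

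Replacing only undosed patients is consistent with the analysis set in section 10 and is not an error. How to analyse dosed patients without an outcome can be left to the analysis plan.

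**Conclusion.** The gap is real and follows from the text alone: neither primary endpoint has a discharge sample, although CT has a discharge rule and section 8.2 implies a last-day assessment. Its size is uncertain. With entry at admission, a mean stay of 6 days and the assumed spreads, about 1 to 11 of 40 patients would have no on-treatment value. The stated allowance of 4 may well be exceeded; the actual margin of 8 is exceeded only under the two widest spreads. The cost is precision and a sample that under-represents fast recoverers. Bias would need an effect of treatment on early discharge. The documents do not support the stronger conclusions that the entry criteria are defective or that the comparison is biased. The point deserves correction because the remedy is cheap and cannot be applied afterwards.

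**What to change.** In 8.3.6 to 8.3.8 and the flow chart, add a rule that mirrors the CT one: *if a patient will be discharged before the next scheduled study draw, a study blood sample is taken before the patient leaves.* This recovers an on-treatment value for nearly all early leavers.

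At the same time, reconcile section 8.2 with the sampling schedule, and the admission-based baseline in 8.3.5 with the inclusion-based baseline in 8.3.6 to 8.3.8.

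The cost is one amendment and one extra 25 ml draw in early-discharge patients. Some of these samples will follow only one or two doses and may show a smaller effect. I would not add a limit on days since admission or a minimum expected stay. Any threshold would have no source in the protocol, an expected-stay rule would rest on a discharge forecast, and both would narrow the population and slow recruitment.
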